#### Functional and perfusion parameters

Both voxel-based and ROI-based 2-sample Student-t test will be applied to compare global ReHo, ALFF/fALFF, CBF between susceptible group and healthy control group with age, sex, education and BMI as covariance. The reference time series for headache-related seed regions will be acquired by averaging the time series for all voxels within them. Correlations of this time-series will be calculated to measure FCs among these regions in each participant. To evaluate group differences in the resting-state topological properties, nonparametric permutation tests were applied [29]. Initially, we will calculate the between-group differences of the mean values for each topological property. Next, an empirical distribution of the difference will be obtained by randomly reallocating every property value into two groups and recomputing the mean differences between the two randomized groups (5,000 permutations) to test the null hypothesis that the observed group differences only occurred by chance. The 95th percentile points of each distribution will be used as critical values for a two-tailed test to determine whether the observed group differences could occur by chance. Non-parametric Spearman correlation will also be performed to delineate a possible relationship between functional alterations and clinical data as well as perfusion alterations and clinical data. Significance threshold will be set at *P* < 0.05 (FWE corrected).

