#### BOLD data

RS-BOLD data will be preprocessed in the toolbox of MATLAB (Data Processing Assistant for Resting-State fMRI, DPARSF; http://www.restfmri.net/forum/DPARSF). SPM8, RS-fMRI data analysis toolkit (REST1.6; http://www.restfmri.net) and graph-theoretical network analysis (GRATNA; https://www.nitrc.org/projects/gretna) will also be selected to deal with the images. The first 10 time points will be discarded to ensure stable magnetization and allow the participants to adapt to the EPI scanning environment. After that, slice timing and head motion will be conducted, and scans with head motion of translation > 3.0 mm or rotation > 3° will be excluded. The functional images will then be spatially normalized to Montreal Neurological Institute (MNI) space using the transformation fields derived from tissue segmentation of individual structural images and resampled to 3 × 3 × 3 mm^3^. The resulting images will be smoothed with 8 mm FWHM isotropic Gaussian kernel. Linear trends will be removed from the image time series, and data will be band-pass filtered at 0.01–0.08 Hz. Finally, nuisance signals such as 24-parameter head motion profiles, white matter, and cerebrospinal fluid signals will be regressed out from each voxel’s time series to exclude non-neuronal sources [28].

Amplitude of low frequency fluctuation (ALFF), regional homogeneity (ReHo) and functional connectivity (FC) values will be estimated in the DPARSFA software that is developed to extract abnormal regions between two groups. Small-world properties and network efficiency will be calculated in the GRETNA software to compare the topological characteristics between two groups.

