#### 3D-pCASL data

For the ASL fMRI data, corresponding CBF images were obtained using an automated image postprocessing tool embedded in the GE healthcare MR-750 system. Subsequently, the CBF images will be spatially normalized to the standard MNI space by using the transformation fields derived from tissue segmentation of structural images and resampled to 3 mm isotropic voxels. The resulting images will be transformed to z scores using Fisher’s transformation approach and then will be smoothed with 8 mm FWHM isotropic Gaussian kernel.

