#### Secondary outcomes measure

Headache level (1–10, VAS), volumetric characteristics (e.g. GMV atrophy), functional characteristics (e.g. ReHo, ALFF/fALFF and FC and abnormalities), topological properties (e.g. small-world properties and network efficiency) and perfusion properties (e.g. CBF changes).

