The functional imaging could reflect the impact of migraine on the brain activity, including neural activity and perfusion condition. RS-BOLD signal had attracted considerable attention in migraine patient to examine potential alterations of brain induced by recurrent migraine attacks. In migraine patients, previous studies have detected various alterations regarding functional connectivity in pain related regions including the periaqueductal gray area (an important region involved in nociceptive processing) [44], as well as insular which is stronger functionally coupled to the dorsal caudal pons and periaqueductal gray area than healthy controls [45]. Other recent studies have reported changed ReHo, ALFF/fALFF or FC in the executive control network [46, 47], and the default mode network [35]. In addition, the functional topologic properties of migraineurs were also observed in precentral gyrus, anterior cingulate gyrus, thalamus and etc. [21, 48]. Previous researches had identified CBF abnormalities as an imaging biomarker in migraineurs, but these CBF studies were all based on single-photon emission computed tomography (SPECT), which is invasive and difficult to generalize in clinical trial [49, 50]. Recently, ASL is an emerging MRI sequence that can be easily performed without contrast injection or any side effects. Some recent studies stressed the significant abnormalities in somatosensory cortex or other brain regions of migraineurs [51, 52], while one study declared that they didn’t see and significant changes [53]. We hope that the impact of the susceptibility of estrogen drop on brain activity could also be reflected in functional imaging.

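### The CBF contrasts, and less directly ALFF and ReHo, are not adjusted for gray matter, so they cannot separate altered perfusion or activity from a gray matter difference in the same region

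*Protocol article*

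**What the plan says.** All places are in the protocol article.

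- **Model.** Under Functional and perfusion parameters, two-sample t tests, both by voxel and by ROI, will "compare global ReHo, ALFF/fALFF, CBF between susceptible group and healthy control group with age, sex, education and BMI as covariance". Gray matter is not among the covariates named there.
- **Maps.** Under BOLD data, images are "resampled to 3 × 3 × 3 mm^3" and then "The resulting images will be smoothed with 8 mm FWHM isotropic Gaussian kernel". Under 3D-pCASL data, CBF images are "resampled to 3 mm isotropic voxels", transformed to z scores and "then will be smoothed with 8 mm FWHM isotropic Gaussian kernel". Neither section describes a partial-volume correction.
- **Outcomes.** Secondary outcomes include "volumetric characteristics (e.g. GMV atrophy"), with functional characteristics and CBF changes listed separately.
- **Reading.** The Discussion states: "The functional imaging could reflect the impact of migraine on the brain activity, including neural activity and perfusion condition". It assigns the long-term structural effect to the T1 and diffusion measures.
- **Available data.** Under High-resolution T1WI data, every participant's T1 scan is segmented into gray matter, white matter and CSF.

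**The concern.** An 8 mm kernel is wider than the cortex (assumed here to be 2.5 to 3 mm thick), so a cortical value in a smoothed map mixes gray matter, white matter and CSF. A woman with less gray matter at a location will tend to show lower CBF there even if flow per unit of gray matter is unchanged. The Background hypothesises that both structure and function differ in these women, so a regional gray matter difference is a possibility the trial itself raises.

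If one exists, the planned contrast cannot tell less tissue from less flow. One structural difference could then be reported under two outcome headings, and the second would be given the wrong physiological meaning. Under Correlation analysis, the most sensitive parameters go forward to an ROC curve, so a mislabelled parameter could be among them.

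The planned steps do not remove this:

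- FWE correction controls chance findings, not a systematic tissue difference.
- The z-transform of CBF does not remove a regional gray matter effect.
- Regressing white matter and CSF signals from the BOLD series denoises each woman's time series. It does not adjust for differences between women in tissue fraction.

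**Working it through.** The protocol gives no figure for this bias. From the documents I use 40 evaluable women per group and two-sided 5% (Subject section). The text gives no effect size; 40 per group at 80% power implies d = (1.960 + 0.842) × √(2/40) = 0.626. Everything marked *assumed* below is not in the documents.

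**1. Tissue mixing.** For a cortical slab of thickness t under a Gaussian kernel of 8 mm FWHM, σ = 8/2.355 = 3.40 mm. The gray matter fraction at its centre is 2Φ(t/2σ) − 1.
- t = 2.5 mm (*assumed*): 0.29.
- t = 3.0 mm (*assumed*): 0.34.
- A 5% thinning lowers these fractions by 4.8% and 4.7%, so smoothing passes the relative loss on almost in full.

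**2. Apparent CBF loss from a 5% gray matter loss, with no change in flow per unit of tissue.** Let g be the gray matter fraction (*assumed* 0.3 to 0.7) and R the gray-to-white perfusion ratio (*assumed* 2 to 3). The signal before loss is g + (1 − g)/R.
- Smallest case (g = 0.3, R = 2, lost tissue replaced by white matter): before, 0.30 + 0.35 = 0.650. After, 0.285 + 0.715/2 = 0.6425. Drop 0.0075/0.650 = 1.2%.
- Largest case (g = 0.7, R = 3, lost tissue replaced by CSF): before, 0.70 + 0.10 = 0.800. After, 0.665 + 0.10 = 0.765. Drop 0.035/0.800 = 4.4%.

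**3. Standardised difference and rejection rate.** With a between-woman coefficient of variation of raw CBF of 15% to 20% (*assumed*), d runs from 1.2/20 = 0.06 to 4.4/15 = 0.29. For a two-sample t test with 40 per group (78 df, noncentrality d√20):

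| d | Rejection rate at nominal 5% |
|---|---|
| 0.06 | 6% |
| 0.29 | 25% |

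This is a single uncorrected test on raw CBF. The protocol sets FWE-corrected P < 0.05 and tests z-transformed maps, so these are not the plan's own error rates. As an illustration, with 10 ROIs (*assumed*) and alpha 0.005 each, the same range of d gives about 0.6% to 6% per ROI, against 0.5%.

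**4. A second route that needs no perfusion ratio or coefficient of variation.** Suppose gray matter differs by dG standard deviations, correlates ρ with the map within groups, and there is no other group effect. The carried-over difference is ρ × dG (both *assumed*; 0.626 is borrowed from the sample size). Rates are for 40 per group without gray matter in the model.

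| dG | ρ | ρ × dG | Rejection rate |
|---|---|---|---|
| 0.3 | 0.3 | 0.09 | 6.8% |
| 0.626 | 0.3 | 0.19 | 13.2% |
| 0.626 | 0.5 | 0.31 | 28.2% |
| 0.8 | 0.5 | 0.40 | 42.4% |
| any | 0 | 0 | 5% |

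In a simulation (3,000 runs per scenario, 40 per group, dG from 0.3 to 0.8, ρ from 0 to 0.7), the model with gray matter as covariate rejected in 4.3% to 5.3% of runs throughout.

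Steps 2 and 3 concern CBF only. No comparable calculation was made for ALFF or ReHo.

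**The case against.** The strongest reply is that the planned contrast is not wrong. For a marker of migraine severity, the total group difference in CBF or ReHo is a legitimate target. If migraine alters structure and flow together, gray matter may lie on the pathway, and adjusting for it answers a different question. This stands. It is why the planned model should be kept, and why the point is limited to what the contrast can be said to show.

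A reader might infer more than the text supports in four places:

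- **That the plan expects atrophy, so double counting will occur.** Atrophy is given only as an example of a volumetric outcome. The structural analysis considers effects in both directions, the Discussion calls earlier volume results mixed, and the Background cites thicker cortex in female migraineurs as well as reduced density. The carry-over is conditional on a difference in the same region.
- **That CBF falls one-for-one with gray matter.** That ignores white matter perfusion and is an upper bound. A 5% loss would then give d = 0.25 to 0.33 and rejection in 20% to 31%, against 6% to 25% above.
- **That all the functional maps are equally exposed.** The mechanism is most direct for CBF, plausible for ALFF and ReHo, and weakest for fALFF, which is a ratio.
- **That the protocol presents the modalities as independent evidence.** It makes no such claim and fixes no model that combines them. Its wording on activity and perfusion is also tentative.

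It can also be said that an article may leave sensitivity models to the full protocol or analysis plan. That has less force here, because the article itself states the covariates and the processing steps. Finally, only secondary outcomes are touched; the primary outcome is white matter integrity (MD, MK and FA).

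**Conclusion.** The concern holds in conditional form. As specified, the CBF contrasts, and less directly those for ALFF and ReHo, estimate a total group difference that may include a gray matter difference in the same region. They are valid as such, but cannot on their own support a statement that perfusion or activity is altered separately from structure.

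The bias is zero if gray matter does not differ or is unrelated to the map. Otherwise its size cannot be fixed from the documents. For CBF, under the stated assumptions, it ranges from negligible to about a fivefold excess on a single uncorrected test (25% against 5%). The gray matter loss, tissue fractions, perfusion ratio and coefficient of variation are all assumptions, and neither the z-transform nor FWE correction enters that figure. The change is worth making, because it is cheap and settles the interpretation; it does not invalidate the planned analysis.

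**What to change.** Keep the planned model. For CBF, ALFF and ReHo, add a second model with each woman's gray matter measure from the T1 segmentation as a further covariate: the voxel-wise map for voxel-based tests and the regional value for ROI tests. fALFF can be included for completeness but is least affected. Report both models. State in advance that a perfusion or functional alteration will be described as distinct from a structural one only where it persists after adjustment, and that the unadjusted result will be described as a total group difference.

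The cost is a few sentences in the analysis section and one extra model per map. No new scans or participants are needed. The downside is that the adjusted result is conservative if migraine lowers both gray matter and flow in the same place. Reporting the two side by side keeps that visible.

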### Subject

All subjects will be provided informed, written consents after the study procedure has been fully explained in detail. Females who match the following criteria would be included in the migraine group: (1) age ranges from 40 to 55 years old; (2) irregular menstrual cycle; (3) suffered from migraine; (4) normal neurological examination. Females who match the following criteria would be included in the HC group: (1) age ranges from 40 to 55 years old; (2) irregular menstrual cycle; (3) not suffered from any kinds of headache; (4) normal neurological examination. Exclusion criteria will be as follows: (1) severe psychiatric disorders, such as dementia, episode, epilepsy, major depression; (2) significant neurological illness, such as significant head trauma, tumor, meningitis or central nervous system (CNS) inflammatory lesions and vascular complications clues; (3) any MRI contraindications; (4) alcohol, nicotine or drug abuse.

Sample size have been estimated by referring to other studies [22, 23]. A sample size of 40 patients per group will be suitable for a power of 0.8 and an alpha significance level of 0.05 (two-side). Considering the drop-out ratio (25%) and unqualified images of included subjects, the total sample size is 55 in each group.

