### Statistical analysis

Statistical Package for the Social Sciences (SPSS) 18.0 (SPSS, Chicago, IL, USA) will be used to analyze the socio-demographic and clinical data. SPM8 and REST 1.8 will be used to analyze the imaging data. All statistical tests were conducted with a significance level of 5%.

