#### Structural parameters

Both voxel-based and ROI-based 2-sample Student-t test will be applied to compare global gray matter (GMV) MK, MD and FA between susceptible group and healthy control group with age, sex, education and BMI as covariance. Moreover, non-parametric Spearman correlation will be performed to delineate a possible relationship between local morphologic alterations and clinical data as well as diffusional alterations and clinical data. Significance threshold, which is corrected for comparison using Family Wise Error (FWE) method, will be set at *P* < 0.05. For each design matrix, significant effects both in the negative and positive directions are considered.

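### As written, the two-tailed permutation test for topological properties cuts at the 95th percentile of the mean difference, which gives a size of about 10%, not the stated 5%

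*Protocol article*

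**What the plan says.** All of this is in the Protocol article.

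- **Statistic** (Functional and perfusion parameters): "we will calculate the between-group differences of the mean values for each topological property".
- **Null distribution** (same section): values are reallocated at random to two groups, "recomputing the mean differences between the two randomized groups (5,000 permutations"). No absolute value is mentioned for the observed or the permuted differences.
- **Cut-off** (same section): "The 95th percentile points of each distribution will be used as critical values for a two-tailed test".
- **Declared level** (Statistical analysis): "All statistical tests were conducted with a significance level of 5" per cent. The Subject section also states a two-sided level: "A sample size of 40 patients per group will be suitable for a power of 0.8 and an alpha significance level of 0.05 (two-side").
- **Role of the outcome** (Outcomes measure): topological properties are secondary. The primary outcome is white matter integrity (MD, MK, FA).
- **Covariates** (Functional and perfusion parameters): age, sex, education and BMI are listed for ReHo, ALFF/fALFF and CBF. None are listed for the permutation test, or for functional connectivity.

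**The concern.** The article does not leave the critical value to a later document. It sets one, and that value does not match the sidedness and level stated elsewhere. The 95th percentile of a mean difference is a one-tailed 5% cut-off. In a two-tailed test, together with its counterpart in the lower tail, it spends 5% in each tail.

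An analyst who follows the sentence tests each topological property at about 10%. One who guesses a different intention tests at 5%. A result between the two cut-offs is then significant or not depending on who runs the code.

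This matters beyond the single test, because the Correlation analysis section takes the most sensitive parameters forward to a ROC curve for grading migraine. A looser threshold lets more chance differences into the pool of candidate markers.

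A smaller, separate matter is confounding. Patients come from a pain clinic and controls from the community, so age, education and BMI may differ between groups. The permutation step, as described, compares plain means.

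**Working it through.** **Inputs.** Level 5%, two-sided (Statistical analysis; Subject). Statistic: difference of two group means, 5,000 permutations (Functional and perfusion parameters). Group size: 40 analysable, and "the total sample size is 55 in each group" recruited (Subject).

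**Step 1: when does the stated 5% come out?** With equal groups, swapping the labels reverses the sign of the difference, so the permutation distribution is symmetric about zero and close to normal at these sizes. A two-tailed test that cuts at percentile p and its counterpart has

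size = 2 × (1 − Φ(z_p)).

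For p = 97.5%, z = 1.960 and size = 2 × 0.025 = 5.0%. So 5% is reproduced if the limits are those of the central 95%.

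**Step 2: the cut-off as written.** For p = 95%, z = 1.645 and size = 2 × 0.05 = 10.0%. The stated 5% is not reproduced.

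**Step 3: simulation.** 10,000 null data sets with normal data and 5,000 permutations:

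| Rule | n = 40 per group | n = 55 per group |
|---|---|---|
| Outside 5th/95th percentiles of the difference | 10.4% | 9.8% |
| Absolute observed difference against 95th percentile of the difference | 10.4% | 9.8% |
| Upper 95th percentile only (one-tailed) | 5.2% | 4.8% |
| Outside 2.5th/97.5th percentiles | 5.1% | 4.9% |
| Absolute difference against 95th percentile of absolute differences | 5.0% | 4.9% |

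The simulation error at a true 10% is √(0.10 × 0.90 / 10,000) = 0.3 percentage points, so 10.4% and 9.8% both agree with 10.0%. Using the upper point alone gives 5%, but that test cannot detect a difference in the other direction and is not two-tailed.

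**Step 4: which results are affected.** In standard-deviation units, the standard error of the mean difference is √(2/n).

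- n = 40: √(2/40) = 0.224. Cut-offs: 1.645 × 0.224 = 0.37 as written, against 1.960 × 0.224 = 0.44 for a true 5% test.
- n = 55: √(2/55) = 0.191. Cut-offs: 1.645 × 0.191 = 0.31, against 1.960 × 0.191 = 0.37.

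Observed differences of about 0.37 to 0.44 SD (n = 40) or 0.31 to 0.37 SD (n = 55) are therefore declared under one rule and not under the other.

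**The case against.** **The wording may only be loose.** Points and values are both plural, the test is called two-tailed, and the level is given as 5% elsewhere. The sentence could be shorthand for the two limits of the central 95%, or for absolute differences. Either gives about 5%. This stands as a possible intention, but it is not what the sentence says. The plural is explained equally well by there being one distribution for each topological property. The FWE threshold that closes the section does not settle it either, since nothing there changes a critical value already fixed for each distribution.

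**A reader might extend the point to the primary outcome.** Structural parameters sets one threshold ("Significance threshold, which is corrected for comparison using Family Wise Error (FWE) method, will be set at" P < 0.05) and adds: "For each design matrix, significant effects both in the negative and positive directions are considered". If that meant two one-sided contrasts at 0.05 each, the error per map would be 1 − 0.95² = 9.75% if independent, and at most 10%. Over three metrics at 10% each it would be 1 − 0.90³ = 27.1%. The article does not support this. It states neither the contrast type nor a separate 0.05 for each direction, and the sentence fits an ordinary two-sided test as well. The 27.1% also assumes that MD, MK and FA are independent, although they come from the same scans, and it mixes in multiplicity: three correct 5% tests already give 1 − 0.95³ = 14.3%.

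**On covariates,** the article is silent about adjusting topological values; it does not rule adjustment out. Functional connectivity has no stated covariates either, so topology is not the only exception.

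**Conclusion.** The point holds for the permutation test of the topological properties, as a fault in the stated decision rule. Taken literally, the rule has a size of about 10%, twice the declared 5%. This rests on two things: the differences keep their sign, as the described steps imply without using that word, and both tails are tested, as the text says.

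It cannot be concluded that the trial's actual error rate will be 10%, because the analysts may apply the central 95%. Nor does the point show doubled error for the structural maps, or 27% over the primary metrics. Only a secondary outcome is affected, and the sample size is not. The missing covariate adjustment is a fair side point for topology, and no more than that.

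**What to change.** **Functional and perfusion parameters, required.** Replace the cut-off with the 2.5th and 97.5th percentiles of the permuted mean differences, or equivalently compare the absolute observed difference with the 95th percentile of the absolute permuted differences. Both give about 5% (4.9% to 5.1% in the simulation). This is one sentence with no extra computing. Fewer borderline topological findings will be declared.

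**Same section, cheap improvement.** Apply the permutation test to topological values adjusted for age, education and BMI, in line with ReHo, ALFF/fALFF and CBF. The cost is one regression per property before permuting.

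**Structural parameters, clarification only.** Confirm in a few words that the FWE-corrected P < 0.05 covers both directions together.

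### The per-property permutation cut-off for network topology does not deliver the FWE-corrected threshold stated at the end of the same section

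*Protocol article*

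**What the plan says.** All statements are in the Protocol article.

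- **General level** (Statistical analysis): "All statistical tests were conducted with a significance level of 5" per cent.
- **What is compared** (Functional and perfusion parameters): "Initially, we will calculate the between-group differences of the mean values for each topological property".
- **Reference distribution** (same section): values are reallocated at random between the two groups, "recomputing the mean differences between the two randomized groups (5,000 permutations" being the stated number.
- **Decision rule** (same section): "The 95th percentile points of each distribution will be used as critical values for a two-tailed test".
- **Closing threshold** (same section, directly after the sentence on Spearman correlations): "Significance threshold will be set at *P* < 0.05 (FWE corrected".
- **Status of the outcome** (Secondary outcomes measure): "topological properties (e.g. small-world properties and network efficiency" are listed there. These are examples; no count of properties appears anywhere.

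**The concern.** The decision rule for topology is complete as written: one difference, one distribution and one cut-off for each property. Nothing in it looks across properties. An analyst who follows it controls the error of each test but not that of the family. The section then claims family-wise control without saying which of its analyses the claim covers (voxel-wise t-tests, permutation tests, correlations or all of them), and without a step that would turn a per-property cut-off into a family-wise one.

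At stake is the reading of a named secondary outcome. A chance difference in one network property could be reported as an abnormality of the migraine group under a section that announces FWE correction. The Correlation analysis section then carries the most sensitive parameters into an ROC analysis, and a chance topology finding would be a candidate for that step.

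**Working it through.** **Inputs from the article.** Significance level 0.05 (Statistical analysis); a cut-off from each property's own distribution, and 5,000 permutations (Functional and perfusion parameters); 40 per group (Subject: "A sample size of 40 patients per group will be suitable for a power of 0.8 and an alpha significance level of 0.05 (two-side").

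**Assumed, because the article is silent.** Number of properties k = 2, 5 or 7; a common correlation between properties from 0 to 0.9. The cut-off is taken as the 95th percentile of the absolute difference, which is the reading that gives 5% two-tailed. Cut-offs at the 5th and 95th percentiles of the signed difference would give 10% per test. That is a separate matter and is not counted here.

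**Step 1: the plan's own figure.** The 95th percentile of the absolute permutation difference gives 5% per property by construction. Simulation with 40 per group (1,500 null data sets, 1,000 permutations each) gave 5.7% and 4.7% in two settings, which is 5% within simulation error. The stated level is reproduced for a single property.

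**Step 2: the family, independent properties.** Chance of at least one false positive = 1 − (1 − 0.05)^k.

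- k = 2: 1 − 0.95² = 9.8%
- k = 5: 1 − 0.95⁵ = 22.6%
- k = 7: 1 − 0.95⁷ = 30.2%

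**Step 3: the family, correlated properties.** Equicorrelated normal statistics, 400,000 draws, two-sided 5% each:

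| Correlation | k = 2 | k = 5 | k = 7 |
|---|---|---|---|
| 0 | 9.8% | 22.6% | 30.2% |
| 0.3 | 9.5% | 20.9% | 27.1% |
| 0.5 | 9.1% | 18.3% | 23.0% |
| 0.8 | 7.9% | 12.7% | 14.9% |
| 0.9 | 7.0% | 10.1% | 11.4% |

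Relative to 5%, the range is 7.0/5 = 1.4 times to 30.2/5 = 6.0 times. Applying the per-property permutation rule itself with k = 7 gave 23.1% at correlation 0.5, in line with the table. At correlation 0 it gave 33.7%, a high draw (standard error √(0.302 × 0.698/1,500) = 1.2 points), so the exact 30.2% is used.

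**Step 4: with a family-wise rule.** One cut-off from the maximum across properties, k = 7: 5.6% at correlation 0 and 4.9% at correlation 0.5, both 5% within simulation error. Bonferroni, independent properties: 1 − (1 − 0.05/k)^k = 4.9% for k = 2, 5 and 7.

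**The case against.** The best defence is that the closing FWE sentence governs the whole section. The Structural parameters section has the same layout: t-tests, then Spearman correlations, then one FWE threshold. The sentence after that threshold speaks of design matrices, so it cannot be meant for the correlations alone. Read the same way here, the sentence reaches the topology tests too. A reader might therefore infer too much in saying that the topology family is tested uncorrected. The article does not settle that, and this part of the defence stands.

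A reader might also infer that a false network finding is several times more likely than 5%. That needs about five or more properties that are not highly correlated. With two properties the rate is at most about double, and at correlation 0.9 it is only about double even for five or seven. The article names only two kinds of property and no number, so the stronger claim is unsupported.

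It can further be said that the list of network measures and the method of correction belong in a fuller document. The list may well be there. But the article does not leave the cut-off open: it fixes one, and that one is not family-wise. A section-wide reading of the FWE sentence does not rescue it. It means that the stated critical value and the stated threshold disagree.

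**Conclusion.** The point holds as an unreconciled conflict within one section. The stated cut-off is per property and unadjusted, and the closing threshold claims family-wise control. On one reading the rule fails to deliver the claim; on the other the topology tests carry no correction. Either way the section needs a change.

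If the cut-off is used as written, with two-tailed 5% per property, the family-wise error exceeds 5% for any two or more properties that are not perfectly correlated: about 7-10% for two, 10-23% for five and 11-30% for seven. These figures rest on assumed numbers of properties and assumed correlations from 0.9 to 0. If a proper family-wise rule is in fact applied, the error is about 5%. The matter concerns a secondary outcome; white matter integrity, the primary outcome, is not affected.

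**What to change.** In Functional and perfusion parameters, replace the per-property cut-off as follows.

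1. In each of the 5,000 reallocations, permute the women's group labels once and apply that permutation to all topological properties, so that their correlation is kept.
2. Compute the absolute standardised mean difference for every property and keep the largest. Standardising is needed because the properties are on different scales.
3. Compare each observed absolute standardised difference with the 95th percentile of that single distribution.
4. State that the FWE threshold covers these tests, and list the properties that form the family.

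A Bonferroni-type cut-off of 0.05/k would also serve. For k = 7 this is 0.05/7 = 0.7% per property, or about 36 of 5,000 permutations, so the planned number still suffices.

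The cost is a few lines of code and no new data or permutations. Each property faces a somewhat stricter cut-off and so loses some power. The maximum-statistic rule loses less than Bonferroni when the properties are correlated. Using the absolute difference also makes clear that the 95th percentile refers to a two-tailed test.
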